### Aim of the study

The primary aim is to assess whether a weight management intervention for obese pregnant women is effective in reducing the women’s Body Mass Index (BMI) 12 months after giving birth.

Secondary aims include:

•to examine whether the intervention leads to lower weight gain during pregnancy;

•to assess whether the intervention leads to fewer complications during pregnancy, at birth and postnatally;

•to examine the impact of the intervention on diet, physical activity levels, health related quality of life, mental health, self-efficacy, social support and breast feeding;

•to examine the child’s weight gain;

•to examine mediators and moderators of change;

•to conduct a cost effectiveness analysis;

•to conduct a process evaluation to examine participant views, drop out, fidelity, duration of participation in the intervention and associated factors.

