### Study intervention

A logic model (shown in Figure 1) describing the theory of the intervention was developed. This illustrates the key inputs, outputs/behaviours and outcomes of the intervention. Participants attending intervention sites will have the opportunity to attend free, weekly, 1.5 hour weight management group sessions from the point of recruitment (between 12 and 20 weeks gestation) up until 6 weeks postpartum. At this time point they will receive one voucher for a free Slimming World session at a ‘normal’ community group. They will also receive two intervention phone calls from the Intervention Midwife at 3 and 6 months postpartum in order to provide longer term support and encouragement. Long term intervention contact helps sustain weight loss [61] and telephone support can be effective in weight loss interventions [62]. Assuming normal gestation of between 37 and 42 weeks and depending on when women were recruited, the intervention period will be up to 56 weeks in total.

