In order to prevent over-exertion, women will be advised to only partake in moderate physical activity and they will be asked to utilise the Borg Scale of Perceived Exertion [66] each time they do any physical activity to monitor levels of exertion. The Borg scale runs from 6 (no exertion) to 20 (maximum exertion), women will be asked to engage in activity that is ‘somewhat hard’ (around 12-14 on the scale). Information regarding warning signs to terminate exercise and when medical advice should be sought will be provided. However, for the majority of women, exercise is safe for both mother and foetus throughout pregnancy and initiating moderate exercise or continuing exercise is recommended in most pregnancies [63].

3) The Midwife component

In addition to the usual NHS midwifery care, the Intervention Midwife will be available to provide advice regarding pregnancy and lifestyle, as well as provide additional support in topics that women may be anxious about like labour choices and breast feeding. Evidence indicates that obese women are less likely than their non-obese counterparts to breast feed [67] and breast feeding is associated with reduced postpartum weight retention [68]. The study is recommending a healthy, balanced and unrestricted diet in pregnancy and therefore foetal weight should not be impaired. Any woman in the intervention group who loses a cumulative 3 kg over the pregnancy will be reviewed by the Intervention Midwife and asked to complete a 7-day food diary to confirm that she is eating a healthy amount of food. If necessary, the Intervention Midwife will refer the participant to their obstetrician. Participant safety will be the responsibility of the Intervention Midwife and any concerns will be referred to an appropriate medical practitioner as per normal protocol within the health care service.

Each session will include the following:

4) Behavioural component

•The weighing session where each woman attending will be weighed.

•New members will be welcomed and achievements of the group reviewed.

•Nutritional advice will be given and the group will discuss topics such as foods to avoid in pregnancy, sharing ideas, recipes, eating out ideas. The women will also be given access to Slimming World resources such as recipe books and magazines.

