**Secondary outcomes**		
Antenatal and birth complications**	Routinely collected data held in patient records	Birth
Pregnancy weight gain	Calibrated adult scales	B, 36w
Waist circumference and waist-hip ratio	Measuring tape	12 m
Child weight centile (adjusted for birth weight and age)	Calibrated baby scales and measuring tape	Birth, 6p, 6 m, 12 m
Admission to neonatal unit	Patient records	Birth
General mental health	General Health Questionnaire (GHQ) 12 [82]	B, 36w, 6p, 6 m, 12 m
Breast feeding intentions	Study-developed questions	36w
Breast feeding behaviour and weaning	Study-developed questions	6p, 6 m, 12 m
Self-reported physical activity	7 Day Physical Activity Recall (7 Day PAR) [83-85]	B, 36w, 6p, 6 m, 12 m
Diet	Dietary Instrument for Nutrition Education (DINE) [86] (plus additional questions on fruit and vegetables, sugar, sweets)	B, 36w, 6p, 6 m, 12 m
Alcohol	Alcohol Use Disorders Identification Test-Consumption (AUDIT-C) [87]	B, 36w, 6p, 6 m, 12 m
Smoking	Study-developed questions	B, 36w, 6p, 6 m, 12 m
Costs	Participant resource use	B, 36w, 6p, 6 m, 12 m
Health related quality of life	EQ-5D (including visual analogue scale) [88]	B, 36w, 6p, 6 m, 12 m

*B = baseline; 36w = 36 weeks gestation; 6p = 6 weeks postpartum; 6 m = 6 months postpartum; 12 m =12 months postpartum.

**gestational diabetes; pre-eclampsia; thrombosis; proportion staying within IOM guidance on weight gain in pregnancy [20]; form of pain relief; birth delivery mode; gestation at delivery; induction of labour; shoulder dystocia, 3^rd^/4^th^ degree perineal tear; postpartum bleeding or thrombosis; Apgar scores.

**Table 2 T2:** Measurement of Mediators

**Mediators**	**Measure**	**When**
Social support	Social Support Exercise and Eating Habits Scales [89] (plus intervention specific social support questions)	B, 36w, 6 m, 12 m
Self-efficacy	Weight Efficacy Lifestyle Scale [90] and Multidimensional Self efficacy for Exercise Scale [91,92]	B, 36w, 6 m, 12 m
Self-regulation	Shortened Self-Regulation Questionnaire [93]	B, 36w, 6 m, 12 m
Motivation	Treatment Self-Regulation Questionnaire (for diet and physical activity) [94]	B, 36w, 6 m, 12 m

(B = baseline; 36w = 36 weeks gestation; 6 m = 6 months postpartum; 12 m =12 months postpartum).

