The primary outcome is maternal BMI at 12 months postpartum. Secondary outcomes will include investigation into the impact of the intervention on gestational weight gain, the child’s weight gain, complications during pregnancy, at birth and postnatally, diet, physical activity levels, health related quality of life, mental health and breast feeding intentions. All staff collecting data will be trained in administering the different outcome measures as well as accurately measuring weight, height and waist and hip circumference. Height will be measured once at baseline and used for all BMI calculations.

Information on both adverse events (AE) and serious adverse events (SAE) will be collected in the study. Trial sites, participants’ GPs and intervention staff are responsible for reporting AEs and SAEs. They may also be reported by participants and by staff completing follow-up. In this trial cohort the following are expected to occur: hospitalisation for normal birth or any antenatal, perinatal or postnatal complications, termination of pregnancy for foetal anomaly and hospitalisation for postnatal depression. Rates of AEs and SAEs are likely to be higher in this group of obese women than the normal population of pregnant women. There are no SAEs expected to be related to the study intervention.

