### Analysis

#### Quantitative analysis

The main analysis will be by intention to treat and will compare the primary outcome of BMI at 12 months postpartum in the intervention and control groups. Multilevel modelling will be used to account for clustering within antenatal unit and individual effects. A two level linear regression model will include baseline BMI (measured at recruitment) as a covariate. Both levels will be considered ‘random effects’ i.e. patients and units are drawn randomly from a larger population of patients and units. Cluster level variables include those used to balance the randomisation: antenatal unit size; proportion of women with BMI +/=30, geographic location and ethnic mix.

For the BMI data, positively skew distributed form is anticipated and will be checked prior to analysis. Log transformation will be considered, not only to deal with the non-normality but to allow interpretation of differences between arms in percentage terms. To further aid clinical interpretation of the intervention effect, analysis of log transformed weight at 12 months postpartum will also be considered, with baseline log weight and log height as covariates. The results can then be expressed in terms of BMI or weight along with a 95% confidence interval. The intra-cluster correlation (ICC) for the primary outcome will be calculated and reported.

Intention to treat analysis will be used for all secondary outcomes. Analysis of secondary outcomes will also use multilevel modelling incorporating baseline scores as covariates where appropriate. Two level linear regression models will be used for outcomes such as pregnancy weight gain and waist-to hip ratio and validated questionnaire scores, while logistic models will be used for clinical event outcomes. 95% confidence intervals for the intervention effect will be calculated. The ICC for each secondary outcome will be calculated and reported.

The impact of individual demographic factors as well as theoretical mediators (self-efficacy, social support, intrinsic motivation and self-regulation) on the intervention effect using interaction terms included in the main analysis models will be examined. Individual demographic variables include age, ethnicity, smoking status, previous weight loss history, psychological wellbeing and social class. We also intend to carry out tests for mediator variables [97].

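### Breast feeding intention is first measured at 36 weeks, after the groups have covered breast feeding, so this secondary outcome cannot be adjusted for, or checked against, its own baseline

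*Protocol article*

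**What the plan says.** Breast feeding is part of the secondary aims, which list "mental health, self-efficacy, social support and breast feeding" among the things the intervention may change (Aim of the study). The text after Tables 1 and 2 names intention as a secondary outcome: "health related quality of life, mental health and breast feeding intentions" (Outcomes).

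Table 1 gives "Breast feeding intentions" one time point, 36 weeks, using study-developed questions. Breast feeding behaviour is recorded at 6 weeks, 6 months and 12 months postpartum. GHQ-12, physical activity, diet, alcohol, smoking, costs and EQ-5D all have a baseline in Table 1, as do all four mediators in Table 2.

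The groups run "from the point of recruitment (between 12 and 20 weeks gestation) up until 6 weeks postpartum" (Study intervention). The Intervention Midwife will "provide additional support in topics that women may be anxious about like labour choices and breast feeding" (the midwife component), and breast feeding is one of the example weekly discussion topics (the behavioural component).

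Secondary outcomes are to be analysed by multilevel models "incorporating baseline scores as covariates where appropriate", with 95% confidence intervals (Quantitative analysis).

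**The concern.** The only antenatal measurement of intention comes after one arm has been exposed to content on breast feeding. Unlike birth events or breast feeding behaviour, intention can be asked at the baseline home visit. Because it is not, the covariate adjustment planned for secondary outcomes has nothing to work with here, and change in intention cannot be described.

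Two things are at stake. The first is precision: women and units differ in intention before any session, and that variation stays in the comparison. The second is protection against differential enrolment. One arm is offered free weekly groups and the other leaflets. Site randomisation says that clinics learn their allocation after site recruitment, and nothing says that women are identified or consented before then. If the offer draws different women, the resulting difference is systematic, and a random effect for unit does not correct it. For this outcome there would be no baseline value to reveal it.

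**Working it through.** **The plan's own figures.** The document gives no rate, ICC or correlation for breast feeding intention, so only the unit sizes can be taken from it. For BMI (difference 1.5, SD 4.5, 80% power, 5% level) the t-based calculation gives 142.5, so 143 per group. Then 286 × 1.4 = 400.4, or 400 women, which is 20 per unit over 20 units. Allowing for 30% dropout, 400 / 0.7 = 571, against 570 stated, or 570 / 20 = 28.5 recruited per unit. These figures reproduce and are not in dispute.

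**Size of chance differences before the intervention.** Assumptions not in the document: intention held by p = 50% to 70% of women, ICC 0.02 to 0.10, m = 20 women per unit, simple randomisation of 10 v 10 units.

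SE of the arm difference = sqrt[2p(1 − p)(1 + (m − 1)ICC) / (10m)]

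- p = 0.7, ICC 0.02: sqrt(2 × 0.21 × 1.38 / 200) = 5.4 points, 95% range ±10.6.
- p = 0.6, ICC 0.02: sqrt(2 × 0.24 × 1.38 / 200) = 5.8 points, 95% range ±11.3.
- p = 0.5, ICC 0.10: sqrt(2 × 0.25 × 2.90 / 200) = 8.5 points, 95% range ±16.7.

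The probability of a chance difference above 10 points runs from 6% to 24%. With 28.5 women per unit the 95% range is ±9.4 to ±15.9 points. A sizeable imbalance in a single trial is plausible.

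**Whether chance differences produce false positives.** In 20,000 simulated trials with no effect, no baseline covariate, p = 0.6 and 20 women per unit:

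| ICC | Unit means, t on 18 df | Units ignored |
|---|---|---|
| 0.02 | 4.9% | 9.3% |
| 0.05 | 5.3% | 15.6% |
| 0.10 | 5.0% | 24.8% |

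The unit-level test stands in for the planned multilevel model. Using a normal reference in place of t gives 6.6% to 6.8%. That excess comes from having few units, not from the missing baseline.

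**Whether a systematic difference does harm.** Suppose recruitment after allocation raised intention in one arm by 5 or 10 points and the shift persisted in full to 36 weeks. The estimate is then biased by the same 5 or 10 points. With no true effect, rejection is 13.7% or 40.1% at ICC 0.02, and 10.5% or 29.6% at ICC 0.05. If only part of the shift persists, the bias shrinks in proportion.

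**Precision gain from a baseline.** For a continuous outcome without clustering and correlation r, the interval narrows by 1 − sqrt(1 − r²): 13%, 20% and 29% for r = 0.5, 0.6 and 0.7 (assumed). With clustering the unit-level correlation matters too. The variance of a unit mean is proportional to ICC(1 − r_u²) + (1 − ICC)(1 − r²)/m. At r = 0.6, ICC 0.02 and m = 20, the unadjusted value is 0.02 + 0.049 = 0.069:

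- r_u = 0: 0.0200 + 0.0314 = 0.0514; narrowing 14%.
- r_u = 0.6: 0.0128 + 0.0314 = 0.0442; narrowing 20%.
- r_u = 0.9: 0.0038 + 0.0314 = 0.0352; narrowing 29%.

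The scale of the questions is not stated. If the answer is yes/no and modelled by logistic regression, these formulas do not apply.

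**The case against.** A reader might infer that any difference between units that existed before the intervention will be reported as an effect. The document does not support that. Units are randomised, so the expected difference is zero, and the planned model carries chance variation between units into the standard error. Excess rejections appear only when units are ignored, which is not the plan. Nor is balance left to simple chance: each block's allocation is drawn from the 25% best balanced on region, unit size, ethnic mix and proportion with BMI of 30 or more, and Quantitative analysis names the same cluster variables. These can remove part of any difference, though none of them measures intention.

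Other points on this side also carry weight. Waist measures are likewise taken without a baseline, although pregnancy is an evident obstacle there. Breast feeding behaviour in this pregnancy cannot have a baseline of its own. The wording on baseline covariates allows for outcomes that have none. The Outcomes section says that completion time was limited to protect follow-up, but that general remark does not explain omitting one or two items from a visit that already takes place.

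On recruitment, the midwife delivering the intervention does not decide whom to approach, and eligible women are to be compared with those recruited. Both help. Neither shows whether enrolled women differed in intention, and knowledge of allocation at the unit is not excluded.

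**Conclusion.** The point holds as a minor design weakness in one secondary outcome. Intention is measured once, after exposure, and cannot be adjusted for its own baseline. Chance differences cost precision and do not raise the false positive rate of an analysis that accounts for units. The size of the loss cannot be computed from the document; the 13%, 20% and 29% figures are illustrations for a continuous, unclustered outcome.

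The more serious possibility is conditional. If women are recruited once units know their allocation, and if that changes who enrols, the breast feeding comparison would be biased by the amount of the shift that persists, with no direct way to detect or correct it. The protocol leaves this open; it does not show that it will happen.

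Because the protocol links breast feeding to lower postpartum weight retention, a reader might also infer that the weight result is compromised. It is not: the primary analysis adjusts for baseline BMI, and breast feeding is not among the Table 2 mediators.

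**What to change.** Add a baseline time point to the intention row of Table 1. Ask the same study-developed question at the baseline home visit, before the first group session. Use the answer as a covariate for intention at 36 weeks and for breast feeding behaviour at 6 weeks, 6 months and 12 months, and report it by arm so that any difference at enrolment can be seen. The cost is one or two more items on an existing baseline questionnaire and a change to the case report form.

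If baseline collection has already passed, adjust the breast feeding analyses for collected predictors such as parity. State with the results that intention before the intervention was not measured and that differential enrolment cannot be excluded for this outcome.

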### Design

The study is a cluster randomised controlled trial; the maternity units, rather than individual participants, are the units of randomisation. This is to minimise risk of contamination of control participants through two potential mechanisms. Firstly, the use of aspects of the intervention with control participants by site midwives who have been trained in study procedures and secondly, the passage of information regarding the intervention between intervention and control participants who are acquainted and attend the same maternity unit.

In addition to receiving usual NHS care, all study participants will be provided with 2 study leaflets: 1) a Food Standards Association eating during pregnancy leaflet detailing foods which should be avoided during pregnancy and 2) an exercise during pregnancy leaflet detailing recommended physical activity during pregnancy and warning signs for when to stop exercise and seek medical attention. Participants attending intervention sites will also receive the HELP Study intervention which is described below. Participants attending control sites will only receive usual care and the leaflets.

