### Protecting against bias

Staff in maternity units who volunteer for the study are likely to be motivated in favour of the intervention, which may result in disappointment in those subsequently allocated to the control group. In order to avoid differential dropout between the experimental and control groups, we will offer the maternity units in the control group the opportunity to complete the training programme after the follow-up period, should the intervention prove to be successful. Careful characterisation of the participating sites, clinicians and patients will be undertaken to judge the external validity of the study findings.

Outcome data will be collected by PIs or trained researchers allied to the project. Due to the nature of the study, it will be difficult for researchers collecting outcome data to be blinded to the allocation of the women; however no staff involved in delivering the intervention will collect follow-up data.

The findings of this study will advance current knowledge in this field, both in terms of weight management interventions for obese pregnant women as well as behaviour change theory. If the trial is successful, this could alter the management of obese pregnant women within the NHS. Potential outcomes of the intervention may include fewer complications in pregnancy and postpartum for both mother and baby as well as less traumatic deliveries. Improvements in the women’s physical and psychological health and self-esteem may also result from attendance at the intervention group sessions, and from the physical activity aspect of the intervention, independent of any weight loss. Benefits to the women may be long lasting. There is evidence that many women retain weight gained during pregnancy. If this intervention is successful this may impact on cumulative obesity developing over several pregnancies. Women will also benefit from expanded healthcare choices (e.g. midwife as opposed to consultant led care) in subsequent pregnancies, if a healthy lifestyle leads to a BMI within normal limits.

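### Intervention staff give one arm an extra adverse-event reporting channel, so reported AEs and SAEs are expected to be higher there even if true rates are equal

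*Protocol article*

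**What the plan says.** The adverse-event paragraph at the end of the Outcomes section (Methods/design) gives three parties a duty to report: it says that trial sites, GPs and "intervention staff are responsible for reporting AEs and SAEs". It adds two voluntary sources: "They may also be reported by participants and by staff completing follow-up". No other rule for eliciting AEs and SAEs is given.

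The arms differ in who is present to report:

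- **Control** (Design): "Participants attending control sites will only receive usual care and the leaflets".
- **Intervention** (Study intervention): women are offered "free, weekly, 1.5 hour weight management group sessions from the point of recruitment (between 12 and 20 weeks gestation) up until 6 weeks postpartum", followed by "two intervention phone calls from the Intervention Midwife at 3 and 6 months postpartum". The groups are run by a midwife and a Slimming World consultant.

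Both arms have usual NHS care and the same four follow-up visits, at 36 weeks gestation and at 6 weeks, 6 months and 12 months postpartum (Follow-up & drop out). Table 1 takes antenatal and birth complications and neonatal unit admission from patient records in both arms.

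**The concern.** One arm has an additional reporter with a formal duty, and the other arm has no counterpart. The extra channel is also suited to picking up minor complaints. Under the intervention description, sessions cover pregnancy ailments and offer one-to-one time with the midwife, and women who miss two or more sessions in a row are contacted.

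A table of reported AEs and SAEs by arm would then mix the effect of the programme with the effect of closer observation. A harmless programme could show an excess. A true excess, for example of complaints arising from the walking programme, could be put down to better reporting. If the source of each report is not recorded at the time, the two explanations cannot reliably be separated later.

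**Working it through.** **1. Who can report, by arm**

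| Source | Status | Control | Intervention |
|---|---|---|---|
| Trial sites | duty | yes | yes |
| GPs | duty | yes | yes |
| Intervention staff | duty | no | yes |
| Participants | may report | yes | yes |
| Follow-up staff | may report | yes | yes |

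Four of the five sources are shared. The asymmetry is added capture in one arm; intervention staff are not the sole reporters there.

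**2. Extra contact offered**

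Inputs from Study intervention: recruitment at 12 to 20 weeks, birth at 37 to 42 weeks, groups to 6 weeks postpartum, last call at 6 months (about 26 weeks). The protocol's own maximum of 56 weeks is reproduced: (42 - 12) + 26 = 56.

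- Fewest weekly sessions: (37 - 20) + 6 = 23.
- Most weekly sessions: (42 - 12) + 6 = 36.
- Plus 2 calls, giving 25 to 38 contacts offered in one arm only.

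Both arms have 4 scheduled follow-up visits plus routine antenatal care. The session numbers are offers, and actual contact depends on attendance.

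**3. Direction of the bias**

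Let p be the true event rate, equal in both arms. Let c be the proportion of events captured by the shared sources, taken as equal in both arms. Let q be the chance that intervention staff report an event the shared sources miss.

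- Recorded rate, control: p × c.
- Recorded rate, intervention: p × [1 - (1 - c)(1 - q)].
- Recorded risk ratio: [1 - (1 - c)(1 - q)] / c = 1 + q(1 - c)/c.

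The ratio does not depend on p, and it exceeds 1 whenever c < 1 and q > 0.

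**4. Illustrative size**

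The protocol gives neither c nor q, so both are assumptions.

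| c | q = 0.1 | q = 0.3 | q = 0.5 |
|---|---|---|---|
| 0.50 | 1.10 | 1.30 | 1.50 |
| 0.70 | 1.04 | 1.13 | 1.21 |
| 0.90 | 1.01 | 1.03 | 1.06 |
| 0.98 | 1.00 | 1.01 | 1.01 |

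Example: c = 0.70 and q = 0.5 give 1 + 0.5 × 0.30/0.70 = 1.21.

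In events, take 570/2 = 285 women per arm and an assumed true rate of 20%, which is 57 women with an event. The expected spurious excess is 57 × (1 - c) × q:

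- c = 0.70: 57 × 0.30 × 0.1 = 1.7, up to 57 × 0.30 × 0.5 = 8.6.
- c = 0.90: 57 × 0.10 × 0.1 = 0.6, up to 57 × 0.10 × 0.5 = 2.9.

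**The case against.** The best case against the point has four parts.

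- **No between-arm AE test is described.** The Quantitative analysis section compares a total count of clinical outcome events by arm and does not mention reported AEs and SAEs. Their tabulation may be set out in a full protocol or SAP that is not shown. This stands, and it limits the point to any by-arm presentation of AEs and SAEs. It does not remove the point, because the unequal reporting duty is a rule the article states.
- **The main harms are protected.** Gestational diabetes, pre-eclampsia, thrombosis, shoulder dystocia, postpartum bleeding, Apgar scores and neonatal admission come from patient records in both arms. This stands in full. A reader might infer that the trial can reach no sound safety conclusion; Table 1 does not support that.
- **Shared capture may be nearly complete for serious events.** The events the protocol expects are mostly hospitalisations, and the sites are maternity units. This stands: at 98% shared capture the ratio is at most 1.01.
- **Reporting an event one learns of is a safety duty.** A reader might see a conflict with Protecting against bias, which says that "no staff involved in delivering the intervention will collect follow-up data". That statement concerns follow-up data. Spontaneous safety reporting by delivery staff does not contradict it, and nothing here argues that they should stop reporting.

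**Conclusion.** The point holds for reported AEs and SAEs, mainly minor or non-hospital events. The direction follows from the reporting rule: with equal true rates and equal capture by the shared sources, the expected recorded rate is higher in the intervention arm unless the shared sources miss nothing or intervention staff add nothing. Nothing in the article corrects for this.

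The size is unknown. For assumed q of 0.1 to 0.5, the recorded risk ratio is about 1.04-1.21 at 70% shared capture, 1.01-1.06 at 90%, and near 1 for well-recorded events. A reader might infer a definite and sizeable excess, but that would require an assumption of poor shared capture that the document does not supply. The result also assumes that sites and GPs in the intervention arm report as fully as those in the control arm. If they left some reporting to the intervention staff, the difference would shrink.

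The change is worth making because it is cheap and has to be in place before events are recorded.

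**What to change.** - Keep intervention staff reporting as it is, for the safety of individual women.
- Record the source on every AE and SAE report, allowing more than one source per event.
- Ask the same AE questions of every woman at the four scheduled follow-up visits, whether or not an event has already been reported. Otherwise the shared-source count could fall short in the intervention arm.
- Base any between-arm AE/SAE comparison on sources used identically in both arms: maternity records, sites and GPs, and those follow-up questions.
- List events known only through intervention staff in a separate table, outside the comparison.

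The cost is one field on the form, slightly longer follow-up visits and a second AE table. One limit remains: where intervention staff prompt a woman to see her GP and the GP then reports the event, it still enters the shared sources.
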